### Neurocognitive functioning

To characterize central nervous system manifestations in patients with SELENON-RM and LAMA2-MD, all cerebral MRI scans that were previously conducted in standard clinical care will be collected and re-assessed for structural abnormalities; if they have not been conducted before, they will not be requested. Furthermore, information on neurocognitive function (education, grade retention, job, social functioning, and participation) will be collected retrospectively from medical history surveys during the natural history study.

### Statistical methods

We will use descriptive statistics to summarize our data. To evaluate disease progression between the follow-up visits of the LAST STRONG and Extended LAST STRONG, mixed-models will be applied. Multiple linear regressions will be used for the exploration of relationships between potential disease modifying variables and disease severity. To investigate relationships between outcome measures, Pearson correlation analysis will be performed. For comparing parameters (e.g. MFM-20/32, accelerometry, bone quality) between ambulant and non-ambulant patients, independent sample t-tests will be performed. Statistical significance will be considered at *p* < 0.05.

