**Methods:**

The Extended LAST STRONG is a long-term natural history study in Dutch-speaking patients of all ages diagnosed with genetically confirmed SELENON-RM or LAMA2-MD, starting in September 2023. Patients visit our hospital twice over a period of 2 years to complete a 5-year follow up from the initial LAST-STRONG study. At both visits, they undergo standardized neurological examination, hand-held dynamometry (age ≥ 5 years), functional measurements, muscle ultrasound, respiratory assessments (spirometry, maximal inspiratory and expiratory pressure, sniff nasal inspiratory pressure; age ≥ 5 years), Dual-energy X-ray absorptiometry (DEXA-)scan (age ≥ 2 years), X-ray of the left hand (age ≤ 17 years), lower extremity MRI (age ≥ 10 years), accelerometry for 8 days (age ≥ 2 years), and questionnaires (patient report and/or parent proxy; age ≥ 2 years). All examinations are adapted to the patient’s age and functional abilities. Disease progression between all subsequent visits and relationships between outcome measures will be assessed.

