Given SELENON-RM and LAMA2-MD’s similar clinical phenotypes, they are well suited to be assessed in a basket natural history study [10, 11]. This can provide valuable insights into their similarities and differences. Currently, no curative treatment options exist for either SELENON-RM or LAMA2-MD; however, promising preclinical studies on novel therapeutic options are currently ongoing [12–21]. Therefore, obtaining natural history data is essential to reach trial readiness. To determine the effectiveness of potential treatment options in clinical trials, it is essential to identify and characterize patients clinically and genetically, in addition to selecting functional outcome measures that correlate with muscle function and are sensitive to temporal changes. For this purpose, the LAST STRONG study, a natural history study aiming to select outcome measures and reach trial readiness, was initiated in 2020 [22]. This study comprised a baseline visit and 1.5-year follow-up of SELENON-RM and LAMA2-MD patients, and the results demonstrated several interesting features of these disorders [10, 11, 23–25]. 90% of both SELENON-RM and LAMA2-MD patients had a low bone density irrespective of age. Despite initiating therapy to improve bone quality as needed, no changes in bone density were observed during the one-year follow-up period. Further, impaired respiratory function was observed in all SELENON-RM patients and in 85% of the LAMA2-MD patients. The SELENON-RM patients showed a progressive decline in respiratory function during 1.5-year follow-up. Additionally, cardiac involvement was observed in a subset of SELENON-RM and LAMA2-MD patients, implying that cardiac follow-up is desirable for optimal management. Based on these results, clear recommendations for clinical care for SELENON-RM and LAMA2-MD patients were formulated and locally implemented in clinical care [26].

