### Study population

No patient registry for LAMA2-MD and SELENON-RM currently exists in the Netherlands. Instead, we have aimed to identify all patients with LAMA2-MD and SELENON-RM mutations in the Netherlands and the Dutch-speaking part of Belgium through contact with genetic diagnostics services, rehabilitation centers, muscle disease experts, and patient organizations.

In the LAST STRONG study, 27 LAMA2-MD patients and 11 SELENON-RM patients were included. Given the high participation rate and minimal loss of follow-up during LAST STRONG, our expectation is to include a total of 35 to 40 patients in the extended study.

The inclusion criteria are identical to those used in the LAST STRONG study: first, a genetic confirmation of LAMA2-MD or SELENON-RM by two recessive pathological variants in the LAMA2 or SELENON gene, respectively, or typical clinical and histological characteristics combined with genetic confirmation in a first-degree relative; and second, patients should be willing and able to complete (part of) the measurement protocol at Radboud university medical center. If patients do not wish or are not able to visit our hospital, they will be offered the opportunity to participate in this study by sharing medical records, completing questionnaires, and undergoing a medical history and physical examination through home visits, video and/or telephone interviews. The only exclusion criterion is an insufficient understanding of the Dutch language.

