• In patients with neuromuscular diseases the motor function can be measured with the MFM-20/32. The MFM is a scale that consists of 20 or 32 items in three different dimensions. D1: standing position and transfers, D2: axial and proximal motor function, D3: distal motor function. MFM-32 is used in patients of 7 years and older. Children between the ages of 2 and 7 will undergo the MFM-20.

4. Graded and timed function tests; age ≥ 2 years: 30 s sit to stand, climb 4 stairs, descend 4 stairs, rise from floor; age ≥ 5 years: 6-Minute Walk test (6MWT) [38–41].

5. Functional Ambulation Classification (FAC); age ≥ 5 years [42].

• The FAC assesses functional ambulation in patients.

6. Brooke and Vignos Scale; age ≥ 2 years [43–45].

• The Brooke and Vignos scale provides ordinal-level data to assess upper- and lower-extremity function.

**Table 1 Tab1:** Examinations performed in the Extended LAST STRONG study

Outcome domain	Assessments	Age

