### Imaging

#### Muscle ultrasound

At both visits, muscle thickness and muscle echogenicity (quantitative grayscale analysis) of the bilateral temporalis, sternocleidomastoid, deltoid, biceps brachii, flexor carpi radialis, flexor digitorum profundus, interosseus dorsalis I, rectus abdominis, rectus femoris, vastus lateralis, gastrocnemius caput medial, soleus and tibialis anterior will be assessed by muscle ultrasound using a Canon Aplio i800 with a PLT-1005BT Probe, following a strictly defined and fixed measurement protocol [46–54]. To measure muscle echogenicity, the mean grayscale level within a manually selected region of interest (ROI) in the ultrasound image will be calculated using an in-house developed software package in MATLAB (version R2022a, Mathworks, Natick, MA, USA). Muscle echogenicity and thickness will be standardized by calculating their z-score: [[measured grayscale level – predicted grayscale level] / standard deviation grayscale]. The predicted grayscale level is determined using a reference equation that includes age, height, sex, and weight [54, 55]. Further, all muscle ultrasound images will be visually evaluated using the semi-quantitative Heckmatt grading scale [56].

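### Pearson correlation is prescribed between outcome measures without exception: it misfits the graded scales and, in one pooled cohort of all ages and both ambulation groups, can reflect shared age or group differences

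*Protocol article*

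**What the plan says.** The Protocol article, Statistical methods, names one method for how outcomes relate to each other: "To investigate relationships between outcome measures, Pearson correlation analysis will be performed". It states no exception by type of scale. The same section applies mixed models to progression between visits, and for comparing parameters "between ambulant and non-ambulant patients, independent sample t-tests will be performed". "Statistical significance will be considered at" p < 0.05.

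Elsewhere the article describes what may enter these correlations:

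- Neurological examination and functional measurements: "The Brooke and Vignos scale provides ordinal-level data to assess upper- and lower-extremity function". The same section grades muscle strength on the MRC scale.
- Muscle ultrasound: "all muscle ultrasound images will be visually evaluated using the semi-quantitative Heckmatt grading scale".
- Abstract, Methods: a "long-term natural history study in Dutch-speaking patients of all ages diagnosed with genetically confirmed SELENON-RM or LAMA2-MD".
- Study population: "our expectation is to include a total of 35 to 40 patients in the extended study".
- Background, on what trial readiness requires: "selecting functional outcome measures that correlate with muscle function and are sensitive to temporal changes".

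The Discussion makes the selection of relevant and sensitive outcome measures a primary aim and expects new imaging biomarkers to emerge.

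**The concern.** There are two separate problems, and they pull in opposite directions.

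**Scale type.** Pearson applied to grade codes treats every step between grades as the same distance. The article's own description of Brooke and Vignos does not support that. Coarse grading also shrinks the coefficient, so graded measures start at a disadvantage in a study meant to choose among measures.

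**Pooling.** When children and adults, walkers and non-walkers are put into one coefficient, two measures can correlate because both depend on age or because both differ between the ambulation groups. A coefficient of that kind can look moderate to strong, and pass p < 0.05, without any association among patients of similar age or ambulation status.

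At stake is which measures are carried forward as outcomes or biomarkers. A measure could be favoured or dropped for reasons unrelated to how well it follows the disease within a patient.

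**Working it through.** The article states no target correlation or power, so there is no figure of its own to reproduce.

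**Inputs from the article**

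- Expected sample 35 to 40 (Study population). The previous cohort was 27 + 11 = 38, used here as n.
- Significance level 0.05 (Statistical methods); two-sided is assumed.

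**Inputs assumed, because the article gives none**

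- Correlation a of each measure with age: 0.3 to 0.8.
- Share w of patients in one ambulation group: 0.3 or 0.5.
- Gap d between group means: 1 to 3 within-group SD.
- Distribution of patients over grades: three patterns, one even, one skewed, one irregular.

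**Step 1. Threshold.** Critical |r| = t / √(n − 2 + t²), with t the 97.5% point on n − 2 degrees of freedom. This gives 0.334 (n=35), 0.320 (n=38) and 0.312 (n=40).

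**Step 2. Graded scales.** With a latent correlation of 0.70:

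| Grade pattern | Pearson, both graded | Pearson, one graded | Spearman, both graded |
|---|---|---|---|
| Even, 5 grades | 0.644 | 0.658 | 0.644 |
| Skewed, 5 grades | 0.600 | 0.584 | 0.566 |
| Irregular, 9 grades | 0.644 | 0.649 | 0.648 |

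Pearson therefore falls to about 0.58–0.66. Spearman loses about as much; what it removes is the dependence on the numbers attached to the grades. For independent graded scales at n=38, Pearson rejects in 4.8–5.0% of samples, so grading does not create false correlations.

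**Step 3. Shared dependence on age.** If two measures each correlate a with age and are otherwise unrelated, r = a².

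- a = 0.3: r = 0.09, significant in about 8% of samples at n=38
- a = 0.5: r = 0.25, about 33%
- a = 0.6: r = 0.36; an observed r of this size has p = 0.026
- a = 0.7: r = 0.49, about 89%; an observed r of this size has p = 0.0018
- a = 0.8: r = 0.64, about 99%

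**Step 4. Two ambulation groups, no correlation within either.** r = w(1 − w)d² / [1 + w(1 − w)d²]. For w = 0.5 and d = 2 this is 0.25 × 4 / (1 + 0.25 × 4) = 0.50. Significance is the share of 5,000 simulated samples of 38.

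| d | r, w = 0.3 | r, w = 0.5 | Pearson significant |
|---|---|---|---|
| 1 | 0.17 | 0.20 | 18–23% |
| 1.5 | 0.32 | 0.36 | 53–65% |
| 2 | 0.46 | 0.50 | 88–96% |
| 3 | 0.65 | 0.69 | about 100% |

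**Step 5. What removes the pooling effect.** Adjusting for group brings the rejection rate back to about 4–5.5% in every setting. Replacing Pearson by Spearman alone does not: at d = 2 it is still significant in 85% (w = 0.3) to 97% (w = 0.5) of samples.

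**The case against.** The strongest reply is that much depends on choices the article does not state. It does not say whether levels or changes are correlated, names no pairs of measures, and does not list Brooke or Vignos as inputs. It is a condensed article, and adjustment or stratification may sit in a fuller document. This stands as a limit: the point rests on the stated choice of Pearson, not on missing detail.

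Several narrower objections also stand:

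- Only Brooke and Vignos are called ordinal. Heckmatt is described as semi-quantitative, and Wong-Baker as a visual analogue scale.
- Ultrasound values are converted to z-scores using age, height, sex and weight, and dynamometry is compared with norms. The Background also reports low bone density regardless of age. The age argument is weaker for these measures.
- Table 1 restricts the graded and timed function tests, including the 6-minute walk, to ambulant patients. The two-group argument cannot apply to them.
- Loss of ambulation reflects severity. Two measures that both separate walkers from non-walkers may share real disease signal, and adjusting it away could remove something of interest.
- The Background names two requirements. Correlation with muscle function can be examined cross-sectionally, and sensitivity to change is addressed by the mixed models.

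The last reply is only partial. A mixed model for each measure shows whether that measure changes; it does not show that two measures change together.

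**Conclusion.** The point holds in two parts. First, Pearson is prescribed without exception in a document that itself describes some outcomes as ordinal. For graded measures the coefficient depends on arbitrary spacing and is attenuated, from 0.70 to about 0.58–0.66 under the assumed grade patterns. Second, in a pooled cohort of this breadth, coefficients can be raised by age or ambulation differences alone. The size runs from negligible (r = 0.09 at an age correlation of 0.3) or below the threshold (about 0.2 at a 1 SD gap) to r = 0.5–0.7 at gaps of 2–3 SD. All of these sizes rest on assumed inputs.

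A reader might infer three stronger things that the article does not support:

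- That the plan correlates raw levels. It does not say.
- That ordinal scales produce the spurious correlations. They attenuate; it is the mix of ages and ambulation groups that inflates.
- That pooled coefficients will be used to claim that a measure tracks progression. Nothing states this.

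**What to change.** Amend the wording in Statistical methods:

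1. Use Spearman or another rank method for ordinal, graded or clearly skewed measures, and keep Pearson for approximately interval measures. Because attenuation remains, do not rank coefficients for coarse scales against those for continuous measures at face value.
2. For measures not already age-standardised, report age-adjusted partial correlations beside the unadjusted ones.
3. Report coefficients within ambulant and within non-ambulant patients as well as pooled, for measures taken in both groups. Showing both leaves the severity signal visible.
4. State whether levels or changes are correlated. Before claiming that a measure tracks progression, also report the correlation of within-patient annualised changes over each patient's available follow-up. Requiring the original baseline would exclude newly recruited patients, who have only the 2-year interval.

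The cost is analysis wording only; no visit or measurement changes, and the last visit is not expected until October 2026. The downside is that adjusted, stratified and change correlations will tend to be smaller and less precise with 35–40 patients. Change correlations may be noisy in particular, since the first 1.5 years showed only minor decline.

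### The ambulant versus non-ambulant t-tests are unadjusted in a cohort mixing two diagnoses and all ages, and for the MFM total score the contrast is partly built in

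*Protocol article*

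**What the plan says.** The Statistical methods section of the protocol article assigns one method to this contrast: "For comparing parameters (e.g. MFM-20/32, accelerometry, bone quality) between ambulant and non-ambulant patients, independent sample t-tests will be performed". It adds: "Statistical significance will be considered at *p* < 0.05". It names no covariate, no visit, and neither the pooled nor the Welch form. The same section plans mixed models for progression between visits, and multiple linear regression for relating possible disease-modifying variables to severity. Neither is said to cover the ambulation contrast.

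The cohort is mixed. Under Study population: "In the LAST STRONG study, 27 LAMA2-MD patients and 11 SELENON-RM patients were included", and for the extension "our expectation is to include a total of 35 to 40 patients in the extended study". The abstract describes "a long-term natural history study in Dutch-speaking patients of all ages". By Table 1, the MFM, accelerometry and DEXA apply from age 2.

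The section on neurological examination and functional measurements gives the MFM dimensions as "D1: standing position and transfers, D2: axial and proximal motor function, D3: distal motor function". It assigns the MFM-20 to children from 2 up to 7 years and the MFM-32 from age 7.

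**The concern.** A two-sample t-test returns one raw difference. If one diagnosis, or one age range, is over-represented among ambulant patients and also differs on the outcome, that difference mixes ambulation with diagnosis or age, and the test cannot separate them. The plan uses covariate-capable models for its other questions but not here.

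The MFM raises a second issue. D1 scores abilities close to the grouping variable, so part of any difference in total score follows from how the groups are formed. One primary aim in the Discussion is to select relevant and sensitive outcome measures, and a partly built-in MFM difference is weak evidence for that. The change of MFM version at age 7 is a further reason to account for age.

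At stake is interpretation. A significant difference in bone quality, activity or MFM could be credited to ambulatory status when some of it belongs to diagnosis, age or the content of the scale.

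**Working it through.** The article gives no sample-size, effect-size or SD figure for this comparison, so there is no figure of the plan to reproduce. It also gives no count of ambulant patients, overall, by diagnosis or by age. Its inputs are 27 + 11 = 38 patients in the preceding study, 35 to 40 expected, and alpha 0.05 (taken as two-sided). Ambulant shares, diagnosis and age effects, and SD ratios below are assumptions.

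**1. Diagnosis.** With no true ambulation effect and a diagnosis effect of d SD, the expected raw difference is

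bias = d × (SELENON-RM share among ambulant − SELENON-RM share among non-ambulant).

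- 14/27 LAMA2-MD and 6/11 SELENON-RM ambulant: 6/20 − 5/18 = 0.300 − 0.278 = 0.022.
- 11/27 and 9/11: 9/20 − 2/18 = 0.450 − 0.111 = 0.339.
- 8/27 and 10/11: 10/18 − 1/20 = 0.556 − 0.050 = 0.506.

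Rejection rates come from 20,000 simulated null datasets per row:

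| Ambulant LAMA2-MD, SELENON-RM | d | Bias (SD) | t-test | Adjusted for diagnosis |
|---|---|---|---|---|
| 14/27, 6/11 | 0.5 | 0.01 | 4.4% | 5.0% |
| 14/27, 6/11 | 1.0 | 0.02 | 3.3% | 5.1% |
| 11/27, 9/11 | 0.5 | 0.17 | 7.2% | 5.0% |
| 11/27, 9/11 | 1.0 | 0.34 | 13.7% | 4.9% |
| 8/27, 10/11 | 0.5 | 0.25 | 10.8% | 5.2% |
| 8/27, 10/11 | 1.0 | 0.51 | 27.9% | 5.2% |

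The share difference can have either sign. With 5 to 7 of 11 SELENON-RM patients ambulant and 18 to 22 of 38 ambulant overall, it runs from 5/22 − 6/16 = −0.15 to 7/18 − 4/20 = +0.19.

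**2. Age.** For 38 patients split 13/25, with age correlated 0.3 to 0.5 in size both with the trait that decides ambulation and with the outcome (5,000 runs each), the t-test rejects a true null in 5.9% (both 0.3) to 21.5% (both 0.5). Adjusted for age, it is 4.7% to 5.5%.

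**3. Error rate of the t-test itself.** Normal data, 38 patients, 100,000 runs, pooled form:

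| Split | SD of smaller group half | Equal | Double | Triple |
|---|---|---|---|---|
| 10/28 | 1.1% | 5.0% | 14.7% | 20.0% |
| 13/25 | 1.9% | 5.0% | 10.8% | 13.9% |
| 19/19 | 5.2% | 4.9% | 5.3% | 5.3% |

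Over 35 to 40 patients the full range is 0.9% to 21.1%. Welch stays at 4.8% to 5.2% throughout. With the same lognormal distribution in both groups at 10/28, pooled gives 4.3% and Welch 6.4%.

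**4. MFM.** D1 covers standing and transfers, which overlap with ambulation. D2 (axial and proximal) and D3 (distal) are not defined by such abilities. The overlap is therefore in one of three dimensions.

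**The case against.** The strongest reply is that the contrast may be purely descriptive. The article speaks only of comparing parameters and claims no effect of ambulation. A raw difference between two clinical groups is a legitimate natural-history result, and an MFM gap would then be expected. That stands as far as it goes, and it is why the unadjusted difference should be kept and labelled. But the article attaches a significance threshold without such a label.

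A reader might also infer more than the documents support:

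- **That the comparison is confounded.** No section gives ambulation by diagnosis or age. With similar shares the bias nearly vanishes. For bone, the Background reports low density in 90% of both diagnoses whatever the age. This weakens the worry for that parameter, although the share with low density does not settle whether means differ.
- **That small, unequal groups distort the error rate.** They do not by themselves: the pooled test holds 5.0% at 10/28 when SDs are equal. Nor do unequal SDs matter much in equal groups. The article states neither group sizes nor SDs, and an independent-samples t-test can be Welch.
- **That only one visit per patient is used.** No visit is named. Returning patients can have up to four visits and new participants two.
- **That non-ambulant patients score at the floor of D1 by definition.** D1 also scores transfers, so the overlap is partial.

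Finally, a condensed article may leave the choice between pooled and Welch to a fuller plan. That is fair for the test form. It does not cover the choice of a method without covariates, which the article states.

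**Conclusion.** The point holds as a limit on interpretation and an easily improved choice of method. As planned, the ambulant versus non-ambulant difference cannot be separated from diagnosis or age if ambulation is unevenly spread over them, and whether it is cannot be told from the article. Under two assumed uneven splits and a 1-SD diagnosis effect, the spurious difference is about 0.3 to 0.5 SD, with false rejection in 14% to 28%. With a 0.5-SD effect it is about 0.2 to 0.25 SD, and with similar shares near zero. For the MFM total score the contrast is partly built in through D1, independently of those assumptions. Error-rate distortion is a minor, conditional matter: it needs the pooled form, unequal group sizes and unequal SDs together, and can then go either way.

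**What to change.** In Statistical methods, estimate the ambulant versus non-ambulant difference with a linear model that includes diagnosis and age, adding a patient random effect if more than one visit enters. Report it beside the unadjusted difference, labelled descriptive. Use Welch for any simple two-group test, checking skewed outcomes first because Welch ran at 6.4% there. Report MFM D1 separately from D2 and D3. A larger model with heterogeneous variances is not needed for 35 to 40 patients.

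Diagnosis and date of birth are already recorded, so the change is in wording and analysis only. With a linear age term, residual degrees of freedom for one visit fall from N − 2 to N − 4, i.e. from 33–38 to 31–36. Precision also falls as diagnosis and ambulation become more correlated. The standard error grows by √(1/(1 − r²)), before any gain from lower residual variance:

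- 11/27 and 9/11 ambulant: r = (9×16 − 11×2)/√(20×18×11×27) = 122/327 = 0.37, about 8% larger.
- 8/27 and 10/11 ambulant: r = (10×19 − 8×1)/√(18×20×11×27) = 182/327 = 0.56, about 20% larger.

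If nearly all patients of one diagnosis are ambulant, the adjusted estimate rests almost wholly on the other diagnosis. Showing the counts of ambulant patients by diagnosis would make that visible.
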